### Statistics

Sample size calculations have been based on an expected improvement of 47 % to 60 % in the proportion of uncomplicated births. Combined with an alpha of 0.05, 80 % power, and a design effect (correction factor due to a stepped-wedge design [21]) of 0.62, a total of 305 pregnant women is necessary for each step. With 13 sites and an expected uptake rate of 25 %, 84 pregnant women/step/site are needed to measure the effects.

Data analysis for the stepped-wedge design will be performed according to an intention-to-treat protocol at the end of the study period, once all sites have at least completed one 3-month intervention period. Individual PRN and ReproQ data will be combined with the different sites. To estimate the intervention effect on the outcome measures, a standard mixed-model approach will be used. The mixed model will incorporate fixed terms for intervention (before versus after), time (3-month period), as well as a correlation of repeated measurements over time as random effects. Hence, the analyses will have the element of a time-series analysis with multiple time points before and after the intervention. Analyses will be performed using SPSS (version 20.0 for Windows: SPSS Inc., Chicago, IL, USA).

Description of the network data by Social Network Analysis (SNA) involves visual analysis of network diagrams produced using a specific software program, NetDraw [22]. This software converts matrices of network data into diagrams and individual nodes using complex algorithms. We will use UNICET v6 [19] to construct the network and obtain network parameters and SPSS 20 (SPSS Inc., Chicago, IL, USA) for statistical analysis.

In addition to log data analysis, the interviews will be audiotaped and transcribed verbatim. The interviews will be independently coded by two persons based on the topic list.

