### Study population

The study will be performed in one regional collaborative organisation in the area of Nijmegen, a Dutch region with an average of 4,500 births a year and more than 230 healthcare professionals involved in maternity care. Community-based midwives are employed in one of 11 independent practices, whereas hospital-based midwives, obstetricians (in training), and paediatricians work in two different hospitals (one providing secondary care and one providing secondary and tertiary care). Maternity care assistants are employed by one organisation and youth health doctors and nurses are employed by one of 14 offices, all of which are coordinated by one organisation.

Each pregnant woman, independently of the gestational age and care setting, will be invited to participate in this study individually; that is, she will be offered the possibility to start her PHR (MyPregn@ncy). All healthcare professionals in the area will be informed of and requested to actively participate in the study.

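### The sample-size figures cannot all hold: 305 women per step over 13 sites at 25 % uptake gives about 94 per site-step, not 84, and a design effect of 0.62 is out of reach at the cluster size that 305 implies

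*Protocol article*

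**What the plan says.** All the sizing is in the protocol article, Methods/design, Statistics.

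- The target is an "expected improvement of 47 % to 60 % in the proportion of uncomplicated births", which is read here as 47 % to 60 %.
- The error rates are given as "Combined with an alpha of 0.05, 80 % power". Sidedness is not stated.
- The adjustment, called a design effect, and the result are given together: "correction factor due to a stepped-wedge design [21]) of 0.62, a total of 305 pregnant women is necessary for each step". Neither an ICC nor the number of women per site and step behind the 0.62 is given.
- The conversion to sites reads: "With 13 sites and an expected uptake rate of 25 %, 84 pregnant women/step/site are needed to measure the effects".

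Other sections fix the layout. Study design gives 13 sites in four groups of three or four, a pre-rollout period, four crossover points and 3-month steps. Table 1 (Measurements) has the registry outcome measured five times, in all women in care in the area. Statistics also promises an intention-to-treat analysis. Study population describes "a Dutch region with an average of 4,500 births a year".

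**The concern.** Two things do not fit. First, the step from 305 to 84 uses only the number of sites and the uptake rate, both stated, and the division does not give 84. Second, a stepped-wedge design effect is not a constant. It depends on the number of steps, the number of measurements, the ICC and the number of women analysed per site and step. If 0.62 is to justify 305 women per step, it should be attainable at 305/13 women per site-step.

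The stated 80 % power rests on this chain. If the links contradict one another, a reader cannot tell which recruitment figure the trial is held to, or what power the planned analysis has. It is also unclear whether the women counted are those who use the record or everyone whose registry data are analysed.

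**Working it through.** **1. Reproduce 305.** Two-sided alpha 0.05, power 0.80, proportions 0.47 and 0.60, mean 0.535.

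n = [1.96 x sqrt(2 x 0.535 x 0.465) + 0.842 x sqrt(0.47 x 0.53 + 0.60 x 0.40)]² / 0.13² = 229.9 per group.

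With continuity correction: (n/4) x [1 + sqrt(1 + 4/(0.13n))]² = 245.04, rounded up to 246. The total is 492, and 492 x 0.62 = 305.04. The figure reproduces. Without the correction the result is 460 x 0.62 = 285; one-sided versions give 224 or 244.

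**2. From 305 to women per site-step.**

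- 305/13 = 23.46 analysed per site-step.
- 23.46/0.25 = 93.8, which is 11.7 % above the stated 84.
- In reverse, 84 x 13 x 0.25 = 273 per step, not 305.
- To keep both 305 and 84, uptake would have to be 305/(84 x 13) = 27.9 %, not 25 %.

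This step needs no ICC and no design formula.

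**3. Can 0.62 arise at 23.46 per site-step?** The usual formula, with k steps, b baseline measurements, t measurements per step, n women per site-step and ICC r, is

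DE = [1 + r(ktn + bn − 1)] / [1 + r(ktn/2 + bn − 1)] x 3(1 − r) / [2t(k − 1/k)].

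Four crossovers and five measurements mean k = 4, b = 1, t = 1, so DE = [1 + r(5n − 1)] / [1 + r(3n − 1)] x 0.4(1 − r). The ICC is not stated, so the whole range was searched:

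| n per site-step | ICC 0.01 | 0.02 | 0.03 | 0.05 | 0.10 | maximum over all ICCs |
|---|---|---|---|---|---|---|
| 23.46 | 0.506 | 0.546 | 0.565 | 0.579 | 0.573 | 0.581 |
| 84 | 0.586 | 0.611 | 0.617 | 0.616 | 0.592 | 0.618 |
| 93.85 | 0.591 | 0.615 | 0.620 | 0.617 | 0.593 | 0.620 |

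A value that rounds to 0.62 first appears at n = 74.

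**4. Cross-check without the closed formula.** The direct mixed-model variance (fixed period effects, random site effect) was computed for 13 sites in groups of 3, 3, 3 and 4 over five periods, and divided by the variance under individual randomisation of the same number per step. At n = 23.46 the maximum over ICC is 0.577 if the group of four crosses over first or last, and 0.592 if it is a middle group. Neither rounds to 0.62. Reading the 21 months as seven 3-month periods lowers the ceiling further, to 0.505.

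**5. Direction.** At 23.46 per site-step the factor would give between 492 x 0.506 = 249 (ICC 0.01) and 492 x 0.581 = 286 women per step; the 0.592 ceiling gives 291. So 305 is on the high side.

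**6. Scale against the region.** 4,500/4 = 1,125 births per 3 months, or 1,125/13 = 86.5 per site if spread evenly. The two readings require 84 x 13 = 1,092 and 305/0.25 = 1,220 women per step.

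**The case against.** **The cause cannot be identified.** This stands. With no ICC and no cluster size stated, 0.62 fits many sizes from 74 upward: 161 to 215 at ICC 0.01, for instance, or 107 to 780 at ICC 0.06. A different layout would also produce it at 23.46: no baseline measurement with ICC about 0.03, or three steps with ICC about 0.003. Both layouts conflict with Study design and Table 1, so they do not rescue the figure, but either could be how it arose. The source cited for the factor is not at hand.

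**The factor error is harmless.** This stands for the factor alone: too high a design effect overstates the need and loses no power. It does not answer the mismatch between 305 and 84. Taking 84 at face value with 25 % uptake delivers 273 per step, below the protocol's own 305.

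**0.62 may suit an analysis of all women.** This is partly right. If everyone in care is analysed, as intention to treat and Table 1 imply, a cluster size of 84 or more is plausible and 0.62 is attainable. But then 305 is not the number analysed per step, and the uptake rate should not be used to scale it up.

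**Stronger readings that a reader might infer.** One is that 84 is correct and 305 is the outlier, because solving n = 492 x DE(n)/13 at ICC 0.03 comes close to 84. The closed formula gives 275 per step and 84.7 per site-step there; the direct variance with the group of four at an end gives 272 and 83.8. The closeness depends on a chosen ICC and site split: over ICC 0.01 to 0.10 the closed formula gives about 74 to 88. It is not evidence of what was done. A second reading is that 0.62 was evaluated before uptake was applied. That is possible, but nothing in the protocol shows it. A third is that the region cannot supply 305 per step. That assumes births spread evenly over sites and 25 % uptake in every period, whereas the protocol counts pregnant women, invites them at any gestational age and describes frequent referral.

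**Conclusion.** The point holds in two parts. The firm part needs no assumption beyond the stated figures: 305, 13 sites and 25 % give about 94 women per site-step, and 84 gives 273 per step, so one of the four numbers is wrong. The second part is that 0.62 cannot be obtained at 23.5 women per site-step for any ICC. The ceiling is 0.58 by the usual formula and 0.58 to 0.59 by direct variance. This rests on reading the design as four crossovers with one baseline and one measurement per step, as Study design and Table 1 describe, and on a model with a random site effect and fixed period effects.

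Which figure is at fault is not established. No loss of power follows from the factor as such. The consequence is that the sample size and the 80 % power cannot be relied on as printed.

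**What to change.** Rewrite the sizing paragraph from one set of inputs:

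- State the ICC assumed and the number of women per site-step at which the design effect was evaluated, together with the numbers of steps and measurements used.
- Say whether the women analysed are the 25 % who take up the record or all women in care. If all women are analysed, the expected difference must be the one across all women, not only among users.
- Recompute and restate together the design effect, the number per step, the number per site-step and the power. The ICC should come from data or a justified assumption, not be chosen so that 84 or 0.62 comes out.
- Compare the restated numbers with the regional average of about 1,125 births per 3 months, about 86.5 per site if evenly spread, and say how any shortfall affects power.

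This costs a reworded paragraph and possibly a less favourable stated figure. The design does not change and no extra women are needed.

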### Measurements

Table 1 presents an overview of all measurements used.

**Table 1 Tab1:** Overview of outcome measures with accompanying methods and measurements

Outcome measure	Study population	Method	Instrument	Time of measurement
Healthcare	All pregnant women in care in the area	Database	Perinatal Data Register	Five times, along all successive steps of the study
Quality of care	All pregnant women in care in the area	Survey	Questionnaire ReproQ	Five times, along all successive steps of the study
Collaboration	All maternity care healthcare professionals in the area	Survey	Social Network Analysis	Baseline and one post measurement
Adoption	All users of MyPregn@ncy	Log format, Survey, Interview	Log data, Questionnaire, Topic list	During and after implementation

The total proportion of uncomplicated pregnancies/births will be based on data from the Dutch Perinatal Registry (PRN). In the Netherlands, more than 95 % of all births and accompanying perinatal outcomes are centrally registered in this large national database [10].

The quality of care from the patients’ perspectives will be measured by an adapted version of the questionnaire ReproQ [15]. This new questionnaire has been developed to evaluate the whole maternity care, regardless of where the care is given [15, 16]. Development of this self-report questionnaire has been based on the 8-domain WHO Responsiveness model, including the following domains: dignity, autonomy, confidentiality, communication, prompt attention, social consideration, basic amenities, and choice and continuity [17]. The original questionnaire consists of two parts with largely identical questions: an antepartum questionnaire and a postpartum questionnaire. Due to considerations of time and response, we will use a combined version of both questionnaires in the present study, 6 to 10 weeks postpartum. Subgroups of participants in the study groups will be invited to complete the ReproQ in every phase of the stepped-wedge design. The results of the questionnaires will be calculated in domain scores and overall scores, ranging from one to four [15]. PRN data and ReproQ data will be collected during each step of the stepped-wedge study.

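### The 80 % power does not belong to the stated intention-to-treat analysis: at 25 % uptake it is about 28 % if non-users gain nothing, and more only with spill-over that the plan does not quantify

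*Protocol article*

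**What the plan says.** All references are to the protocol article.

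- **Sizing (Statistics, first paragraph).** The target is a 13-point gain in uncomplicated births, from 47 up to 60 %. The test level is 0.05 and the power 80 %, and a stepped-wedge correction factor of 0.62 is applied. The plan concludes that "a total of 305 pregnant women is necessary for each step". It next allows for the number of sites, 13, and for "an expected uptake rate of 25" %, and so arrives at 84 women per step per site.
- **Analysis (Statistics, second paragraph).** "Data analysis for the stepped-wedge design will be performed according to an intention-to-treat protocol at the end of the study period". The mixed model has a fixed intervention term that contrasts before with after, and a term for the three-month period. The intervention term therefore follows the site's status, not a woman's own use of the record.
- **Population (Measurements, Table 1).** For the primary outcome, taken from the perinatal register, the population is "All pregnant women in care in the area".

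No section reduces the 13-point effect for women in intervention periods who do not take up the record.

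**The concern.** The two paragraphs under Statistics use different populations. The sizing counts users: it finds the number needed for the full 13 points and then enlarges it so that roughly that many users are present. The analysis counts every birth at a site once the site has crossed over, and an expected 75 % of those women are non-users.

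When an effect is diluted by a factor of 0.25, the required number grows by about 1/0.25² = 16. Dividing by 0.25 once allows for a factor of 4 only.

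At stake is how the primary result will be read. Readers of a null result will take it that the trial had 80 % power for the effect it was designed around, when under the stated analysis its chance of detecting that effect may have been nearer one in four.

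**Working it through.** **Inputs.** From Statistics: 47 % and 60 %, alpha 0.05, 80 % power, design effect 0.62, 305 per step, 25 % uptake, 84 per step per site. From Study design: 13 sites, four groups, three-month steps. From Table 1: five measurement occasions. From Study population: 4,500 births a year. Assumed: a two-sided test (sidedness is not stated, but two-sided reproduces 305) and the intracluster correlation (ICC, not given), taken over a range.

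**1. The plan's figure.** Two proportions, 0.47 against 0.60, two-sided with continuity correction: 246 per arm. 2 x 246 x 0.62 = 305.04. The 305 reproduces.

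**2. The inflation.** 305 / 13 / 0.25 = 93.8, so 305 users would need 94 per site. The stated 84 gives 84 x 13 = 1,092 births per step and 1,092 x 0.25 = 273 users. The actual inflation is 84 / 23.5 = 3.6-fold, roughly the 4-fold that one division by uptake would give. This slip is separate and does not drive what follows.

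**3. The difference across all births.** With uptake *u* and non-users gaining a fraction *s* of the user effect, the difference is 13 x [*u* + (1 - *u*) x *s*] points. For *u* = 0.25 and *s* = 0 it is 3.25 points (47 % to 50.25 %).

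**4. Power on the plan's own convention.** Equivalent number per arm: 1,092 / 0.62 / 2 = 881. Power for 3.25 points is 27.6 % (26.0 % with continuity correction). At 94 per site it is 30 % (29 % with correction).

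**5. Cross-check.** A stepped-wedge mixed model was used (random site effect, fixed period effects, groups of 3, 3, 3 and 4 sites, five periods, 84 births per site and period).

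| Uptake | Non-users' gain, as share of user effect | Difference, all births | Power, design effect 0.62 | Power, stepped-wedge model, ICC 0.01-0.10 |
|---|---|---|---|---|
| 25 % | none | 3.25 points | 28 % | 28-29 % |
| 25 % | one tenth | 4.2 points | 43 % | 43-45 % |
| 25 % | one third | 6.5 points | 78 % | 78-81 % |
| 50 % | none | 6.5 points | 78 % | 78-81 % |

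For the first row:

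- At ICC 0.005 the model gives 31 %, so the range for ICC 0.005-0.10 is 28-31 %. It gives 36 % at 0.001.
- With seven periods (the 21 months under Study design, in three-month steps) it gives 32-33 % for ICC 0.01-0.10.
- If the correlation between periods within a site is 0.8 of that within a period (an assumption), it gives 13-26 % for ICC 0.01-0.10.

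**6. Detectable difference and required number.** The standard error is about 2.3 to 2.4 points. At 80 % power the detectable difference is (1.96 + 0.84) x 2.3 to 2.4, or about 6.5 points. For 3.25 points, 3,712 per arm x 2 x 0.62 = 4,603 women per step are needed (354 per site), against 4,500 / 4 = 1,125 births per three months in the region.

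**The case against.** **Non-users may benefit.** This is the strongest objection. Study design describes an intervention implemented at cluster level, Intervention includes the professionals, and Background expects better collaboration among them. Women who never open the record could gain by that route. This stands. A reader might infer that 28 % follows from the plan's figures alone, or that 13 points cannot be the effect across all births because users would have to move from 47 % to 47 + 13 / 0.25 = 99 %. Both inferences need zero effect in non-users, which no section states. The 28 % is therefore the case without spill-over. The plan neither claims nor quantifies an amount of spill-over that would restore 80 %, and on the table above it would take about a third of the user effect.

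**The 13 points may be meant for all births.** Then no inflation for uptake is needed, and power at 84 per site exceeds 99.9 %. The inflation itself argues against this reading, but the plan should say which one it intends.

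**Uptake may mean consent or available data.** Then one division would be right. This reading is weak. Study population equates taking part with being offered the record, and the primary outcome comes from the register. Table 1 is not decisive alone, since it names the same population for the ReproQ questionnaire, to which only subgroups are invited.

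**305 may be a whole-trial total.** Five steps of 1,092 births would then give about 86 % power for 3.25 points. The text says the number is per step, and the five-period model, which uses all the births, gives 28-31 %.

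**Conclusion.** The point holds as a mismatch between sizing and analysis. The inflation treats the 13 points as an effect in users, the analysis estimates an effect across all births, and the stated 80 % does not carry over from one to the other.

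The size depends on what non-users gain: about 28 % power if nothing, about 43-45 % if a tenth of the user effect, about 80 % if a third. These figures rest on 25 % uptake, 84 births per site and step, and the plan's design effect or an assumed ICC in the stated range. Within-site correlation that decays over time would lower them.

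A reader might go further and call a null result uninformative. The documents do not support that. With a standard error near 2.4 points, a non-significant estimate is at most about 1.96 x 2.4 = 4.7 points, and its upper 95 % limit is at most about 9.4. Under the plan's design effect, a null would still exclude a 13-point improvement across all births. It would say little about the user-only effect that the sizing assumes. Nor do the documents point to a users-only primary comparison, since they specify intention to treat.

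**What to change.** 1. Keep intention to treat on all register births as the primary analysis.
2. State whether 47 % to 60 % refers to users or to all births. Define uptake, and say that it is not an analysis filter.
3. Replace the 80 % statement with power for the diluted effect over a range of uptake and spill-over (about 28 % at 25 % uptake and about 78 % at 50 %, both without spill-over). Add the detectable difference of about 6.5 points and the ICC assumed.
4. Reconcile 84 with 94 women per site.
5. Optionally, add a complier-average estimate as a supportive analysis. Using site allocation as the instrument requires that the record act only through a woman's own use, which the collaboration hypothesis puts in doubt, so that assumption must be stated. It also needs use to be linked to outcomes or summarised by site and period. The article describes log data on accounts and logins but no link to register records.

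The cost is a rewritten sample-size paragraph and a less favourable stated power. No extra women are needed, and the region could not supply the roughly 4,600 per step that 80 % power for 3.25 points would take.

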### Study design

The effects of the implementation of a PHR in maternity care on patients and professionals will be identified in a stepped-wedge, cluster-randomised, controlled trial. This type of trial is suitable for studying the effects of a new intervention, which is implemented at the cluster level, but experienced and measured by its impact on individuals [11, 12]. In essence, a stepped-wedge trial randomly allocates clusters to groups that crossover from a control condition to an intervention at different crossover points. In the present study, all healthcare professionals, working at 13 sites (11 community-based midwife practices and two hospitals, comparable in the number of patients) agreed to participate. Following baseline measurements, sites will be randomly assigned to four groups, containing three or four sites. The two hospitals are randomly allocated to group 1 and group 2; groups 3 and 4 contained only community-based midwife practices. The length of time between the two successive crossover points is 3 months. The total trial duration is 21 months. Figure 1 illustrates the study over time, including a pre-rollout period, four crossover points, and a post-rollout period. At the start of the study, all sites belong to the control group; at the end of the study, all sites belong to the intervention group. Data collection will be performed in all steps along the trial, coinciding with all four crossover moments.

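### The four sample-size figures (305 women per step, 13 sites, 25 % uptake, 84 women per step per site) do not agree: the first three give 94, not 84.

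*Protocol article*

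**What the plan says.** The sample-size paragraph in the Statistics section of the protocol article runs as one chain.

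- Effect: an "expected improvement of 47 % to 60 % in the proportion of uncomplicated births".
- Error rates: "Combined with an alpha of 0.05, 80 % power".
- Stepped-wedge correction: a "design effect (correction factor due to a stepped-wedge design [21]) of 0.62".
- Result per step: "a total of 305 pregnant women is necessary for each step".
- Conversion to sites: "With 13 sites and an expected uptake rate of 25" %, the article concludes that "84 pregnant women/step/site are needed to measure the effects".

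Two other sections bear on the last link. Study design confirms 13 sites (11 midwife practices and two hospitals) and 3 months between crossover points. Study population describes the area as "a Dutch region with an average of 4,500 births a year". The article states no further inflation or deflation factor.

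**The concern.** The last link looks like a plain division of the per-step total by the number of sites and the uptake rate, but dividing does not give 84. The per-site figure is the recruitment requirement a reader would use to judge feasibility, and here the discrepancy falls across the supply limit. At 84 per site the requirement fits just under the region's average births in 3 months. At the figure the other inputs imply, it does not. So a reader who trusts 84 would conclude that the region can supply 305 users per step, while a reader who trusts 305 and 25 % would conclude that it cannot.

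**Working it through.** **Inputs.** Statistics: 47 % v 60 %, alpha 0.05, power 80 %, design effect 0.62, 305 per step, 25 % uptake, 84 per step per site. Study design: 13 sites, 3-month steps. Study population: 4,500 births a year on average. Sidedness is not stated; I assume two-sided.

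**1. Reproduce 305.** The two-proportion formula with continuity correction gives 246 women per arm. Both arms with the design effect: 2 × 246 × 0.62 = 305.04. The 305 reproduces. Without the correction, 230 per arm gives 2 × 230 × 0.62 = 285.2, which does not match.

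**2. Reproduce 84.** 305 / (13 × 0.25) = 305 / 3.25 = 93.85, so 94. The 84 does not reproduce, and a gap of 10 is too large for rounding.

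**3. Other routes to 84.**

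| Variant | Women per step per site |
|---|---|
| No continuity correction, 285.2 / 3.25 | 87.8 |
| Unpooled variance (228 per arm), 282.7 / 3.25 | 87.0 |
| One-sided, without / with continuity correction | 69.1 / 75.2 |
| 25 % read as dropout, 305 / 13 / 0.75 | 31.3 |
| 11, 12 or 14 sites at 25 % | 110.9, 101.7, 87.1 |

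None gives 84.

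**4. Read backwards.** 84 × 13 × 0.25 = 273 women per step, 32 fewer than 305 (32 / 305 = 10.5 %). For 84 to yield 305, uptake would have to be 305 / (13 × 84) = 27.9 %, or there would have to be 305 / (0.25 × 84) = 14.5 sites.

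**5. Supply per 3-month step.** 4,500 / 4 = 1,125 births, or 1,125 / 13 = 86.5 per site.

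- At 84 per site: 84 × 13 = 1,092, which is 97 % of 1,125.
- At 94 per site: 94 × 13 = 1,222, which is 109 % of 1,125.
- Users reachable at 25 %: 1,125 × 0.25 = 281, or 24 short of 305.
- Uptake needed to reach 305 from all births: 305 / 1,125 = 27.1 %.

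**The case against.** The mismatch itself has no answer in the article. The case on the other side concerns what follows from it, and much of that stands.

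*Which figure is wrong is unknown.* 305 / 13 / 0.28 = 83.8, which rounds to 84, so a misprinted uptake rate explains the mismatch as well as a misprinted 84 does. On that reading 1,092 women fit within 1,125 births. The supply shortfall is therefore conditional on 305 and 25 % both being right.

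*The uptake accounting may not apply to the primary analysis.* Table 1 takes the primary outcome from the perinatal register for every woman in care in the area, and the Statistics section specifies intention to treat. On that basis the women analysed per step are close to all registered births, not the quarter who open a record. The shortfall exists only if users are what is counted.

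*The supply limit is soft.* The 4,500 is an average and the 25 % an expectation. Women are invited at any gestational age, so more are in care than give birth in one quarter, and referred women may be seen at two sites. The pre- and post-rollout periods may also exceed 3 months. However, the primary outcome is scored once per birth and 305 is required in each step, so this softens the limit for the 3-month steps without removing it.

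*A reader might infer that the trial's power falls to about 75–77 %.* That is what the continuity-corrected formula gives when 273 or 281 women are treated as the whole sample (78–79 % without the correction). The article does not support this as the power of the trial. The figure describes one step's users only, whereas Table 1 has register outcomes collected at five times for all women in care.

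**Conclusion.** The four figures cannot all be right. Taking 305, 13 and 25 % as given, the per-site requirement is 94 and the stated 84 is 10 too low, or 94 × 13 − 84 × 13 = 130 women per step over all sites. Taking 84, 13 and 25 % as given, the yield is 273, not 305. This rests only on figures printed in the article.

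The feasibility part is conditional. If 305 and 25 % stand, users are the unit counted, and births run at the stated average, the requirement exceeds average births in a 3-month step by about 9 % (1,222 v 1,125), and about 281 of 305 users are reachable. If the uptake was meant to be about 28 %, or if all registered births are analysed, that shortfall disappears.

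The stronger conclusion, that the region cannot deliver 80 % power for the trial, is not supported. Severity is moderate: the wrong figure sits in the sample-size statement, but the 84 governs no analysis or inclusion rule, and all sites and all women in the region are already included.

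**What to change.** 1. Reconcile 305, 13, 25 % and 84. If 305 and 25 % are right, correct 84 to 94; otherwise correct the misprinted input and show the division.
2. State the births available per 3-month step: about 1,125 in the region, or 86.5 per site on average.
3. State which accounting applies. Either the 305 counts users, in which case say whether it is met at the expected uptake, or the intention-to-treat analysis uses all registered births, in which case drop the uptake inflation and say so.
4. Do not replace the stated power with 75–77 %.

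The cost is one corrected number and two sentences. Nothing in the design, the data collection or the planned model has to change.
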